### Potential somatic factors and biological predictors

#### Weight gain and metabolism

Considering that primary care physicians typically focus on somatic symptoms, it is important to note that unipolar depression is associated with a range of comorbidities such as increased cardiovascular risk, adiposity, dyslipidemia, as well as high blood pressure and hyperglycemia, resulting in an increased cardiovascular risk [18]. These somatic symptoms might be the main focus of primary care physicians when diagnosing and treating patients, making it even more crucial to consider the possibility of depression and its potential impact on overall health. In fact, the presence of a metabolic syndrome, which is defined as a combination of obesity, low HDL cholesterol, high blood pressure, and elevated blood sugar levels, has been linked to unipolar depression [19]. The metabolic dysregulation in unipolar depression is associated with immunologic changes, which might only affect a clinical subgroup of patients, namely patients with higher childhood trauma scores and rather atypical features of unipolar depression [20, 21]. The link between increased body fat percentage and chronic low-level inflammation [22], childhood trauma, depression, and low physical activity is well documented [22–24]. Increased body weight is associated with decreased well-being, vitality, and quality of life [25]. Weight gain may be followed by the development of metabolic syndrome [26], which increases the risk of cardiovascular disease, autonomous dysregulation [27] and type II diabetes. Patients with unipolar depression have a higher likelihood to suffer from hypercholesterolemia and triglyceridemia compared to their non-affected peers. This association was especially present in women and in patients older than 40 [28]. A lower expression of brain-derived-neurotropic-factor (BDNF), which is associated with mood disorders like unipolar depression, could be observed in mice that were put on a hypercaloric diet [29]. Another hormone that might play an important role in the context of depression and a dysregulated metabolism is Insulin-like Growth Factor—1 (IGF-1). The expression of IGF-1 is influenced by nutrition, BMI and insulin levels, as well as age, sex, and ethnicity. While IGF-1 is mainly known for being a growth hormone that also increases testosterone production [30], evidence further suggests that IGF-1 plays an essential role in dementia, cardiovascular, and metabolic diseases [31, 32]. Elevated IGF-1 levels may increase the risk of developing depression [33, 34], but seems to also mediate the rapid antidepressant effect of ketamine [35, 36].

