### Outcome assessment

#### Primary outcome

Our primary outcome is the development of an algorithm that predicts the severity of unipolar depression with biological markers. We will use the routine blood laboratory markers, as well as the HRV data and only include single items concerning the self-rating questionnaire, if necessary. We hypothesize that IGF-1 and AAT-1 will be biological markers that facilitate diagnosing unipolar depression and hence will mainly drive the prediction together with the HRV data. We will use the PHQ-9 and the MADRS at baseline and follow-up to measure changes in depressive symptomatology as well as their severity [48]. Supervised algorithms like decision trees and support vector machines will be used to determine which factors drive the severity of depression at inclusion.

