#### Secondary outcomes

Furthermore, we will implement a prospective algorithm predicting the severity of the participants' depressive symptomatology after one year. The results will be compared with the expertrating conducted at baseline. To ensure generalizability we will test the cross-sectional algorithm on the follow-up data. Further we will conduct a structural equation model (SEM) analysis at inclusion to better understand the underlying mechanisms that drive unipolar depression. Unsupervised cluster algorithms will be used to detect biomarker driven subtypes.

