#### Mediating variables

Lifestyle factors, personality traits, and personal history are considered to be mediating variables. We will consider blood pressure, medication, age, and gender as confounding factors. The breathing rate is not monitored [105].

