### Planned data analyses

Categorical data will be one-hot-encoded if suitable and summarized with percentages and confidence intervals. For ordinal data the median will be given as well as the interquartile range and for continuous data we calculate the mean as well as the standard deviation and the confidence intervals. Demographic and baseline characteristics in the study arms will be compared with suitable statistical tests. Since multiple comparisons will be performed significant *p*.values will be reported false discovery rate corrected [107]. With the cross-sectional data at inclusion a SEM analysis will be conducted [108]. Furthermore, we will investigate the predictive value of baseline biological parameters for change in depressive symptomatology. In addition, we will design a classification algorithm using all relevant data detecting which participant is depressed. This approach involves the implementation of multiple supervised machine learning algorithms to thoroughly assess their performance. We will evaluate each algorithm during the analysis stage and subsequently select the one that yields the most favorable results. These algorithms may include, but are not limited to, support vector machines, decision trees, and neural networks. Each of these algorithms will be carefully applied and evaluated in the context of our research question. Furthermore, we will use multimodal stacked algorithms to assess the generalizability of different clinical questionnaires and biomarkers separately. To ensure the robustness of our algorithm selection and model performance assessment, we will employ a leave-site-out nested cross-validation approach in each model. This mitigates the risk of overfitting and ensures generalizability. Since the eventual goal of our algorithm is the implementation in a clinical context and to guide general practitioners, we plan to develop a sequential prediction model, which reduces the number of required data modalities and diagnostic uncertainty, as described by Koutsouleris et al. [109]. Sequential stacking models can be used to reduce the data required to produce optimum prediction scores. This method can greatly increase clinical applicability since physicians will be only asked for additional information if needed to achieve satisfactory predictive accuracy [109].

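### The primary severity algorithm has no base model of routine GP data, so IGF-1 could appear as a driver only because it tracks age, sex or BMI

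*Protocol article*

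**What the plan says.** The Primary outcome section of the protocol article states: "Our primary outcome is the development of an algorithm that predicts the severity of unipolar depression with biological markers". On predictors it says: "We will use the routine blood laboratory markers, as well as the HRV data and only include single items concerning the self-rating questionnaire, if necessary". Age, sex and BMI are not listed. The hypothesis follows: "IGF-1 and AAT-1 will be biological markers that facilitate diagnosing unipolar depression and hence will mainly drive the prediction", jointly with HRV. Decision trees and support vector machines are then to show which factors drive severity at inclusion.

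Under Weight gain and metabolism the article says: "The expression of IGF-1 is influenced by nutrition, BMI and insulin levels, as well as age, sex, and ethnicity". The same section links depression to adiposity.

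Other parts of the article bear on the point:

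- **Mediating variables:** "We will consider blood pressure, medication, age, and gender as confounding factors". BMI is not named, and how these variables enter an algorithm is not stated. Lifestyle factors are classed as mediating.
- **Secondary outcomes:** for the one-year prognostic algorithm, "The results will be compared with the expertrating conducted at baseline".
- **Planned data analyses:** "we will use multimodal stacked algorithms to assess the generalizability of different clinical questionnaires and biomarkers separately". The section also plans a classifier of depressed versus not depressed, leave-site-out nested cross-validation, and a sequential model that asks for further data only when needed. The algorithm is meant to guide general practitioners.
- **Study aims and hypotheses; Methods and design; Strengths and limitations:** there are 475 depressed participants, 425 without depression, and 50 healthy controls with no medical history. About 90% of the cohort is to come from GP offices. Flyer recruitment of healthy participants may attract people who are fit and watch their weight.

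**The concern.** The hypothesis has two parts: the markers help diagnosis, and they are what drives the prediction. Both are to be read from an algorithm whose listed inputs leave out variables that, by the article's own account, determine IGF-1. A model given IGF-1 but not age, sex or BMI will use whatever IGF-1 carries about them. If those variables differ with depression status or severity, IGF-1 gains importance even if it says nothing further about depression.

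The intended user is a GP, who knows age, sex and weight before any blood is drawn. The useful question is therefore what the panel adds to that knowledge. Total accuracy and a ranking of drivers do not answer it. Leave-site-out validation does not help either, because a proxy for age or BMI can hold up equally well at a new site.

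**Working it through.** **1. The article's own figure.** The only sample-size figure is 870, for the structural equation model (Power calculation: effect 0.15, power 0.90, alpha 0.05, 5 latent variables). The Westland lower bound reproduces it:

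- Five latent variables give 5 × 4 / 2 = 10 pairs, and the Šidák-adjusted alpha is 1 − 0.95^(1/10) = 0.00512 (two-sided z = 2.800; z for power = 1.282).
- H = (0.15 / (2.800 + 1.282))² = 0.00135.
- With ρ = δ = 0.15: A = 1 − ρ² = 0.9775, B = ρ·asin(ρ/2) = 0.0113, C = ρ·asin(ρ) = 0.0226, D = A/√(3 − A) = 0.6873.
- t = A(π/6 − B + D) + H = 1.174.
- n = [t + √(t² + 4AH(π/6 + √A + 2B − C − 2D))] / 2H = 869.2, rounded up to 870.

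This sizes the structural equation model, not the primary algorithm, so the point here does not turn on it.

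**2. How a proxy arises.** Suppose a covariate (age, say) differs by d SD between depressed and non-depressed participants, and IGF-1 correlates r with it but has no effect on depression beyond it. Then IGF-1 differs by |r|·d SD between groups, its own AUC is Φ(|r|·d/√2), and the covariate's AUC is Φ(d/√2). The documents give neither r nor d. Both are assumptions below.

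| r | d | AUC, IGF-1 alone | AUC, covariate alone |
|---|---|---|---|
| any | 0 | 0.50 | 0.50 |
| 0.20 | 0.25 | 0.51 | 0.57 |
| 0.45 | 0.50 | 0.56 | 0.64 |
| 0.63 | 0.80 | 0.64 | 0.71 |

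In a simulation (training on 475 v 475, testing on 2,000 v 2,000, 200 repetitions, r² of 0.2 and 0.4, d from 0 to 0.8), adding this null IGF-1 to a model that held the covariate changed AUC by 0.000 to −0.002. A base model therefore exposes the proxy.

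**3. A given age gap.** Assume an age SD of 14 years, r of 0.4 to 0.6 and a 6-year gap between groups of 475.

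- IGF-1 difference: 6/14 × 0.4 = 0.171 to 6/14 × 0.6 = 0.257 SD.
- z = difference/√(2/475) = 2.64 to 3.96.
- AUC = 0.55 to 0.57; age alone gives Φ(0.429/√2) = 0.62.

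**4. Can the healthy controls produce that gap?** They are 50 of the 50 + 425 = 475 non-depressed participants. To shift the group mean by 6 years on their own they would have to be 6 × 475/50 = 57 years younger than the rest, but eligibility at 18 to 70 spans 52 years. If they were 15 years younger, the shift would be 15 × 50/475 = 1.58 years:

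- IGF-1 difference: 1.58/14 × 0.4 = 0.045 to 1.58/14 × 0.6 = 0.068 SD.
- z = 0.70 to 1.04.
- AUC = 0.51 to 0.52.

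A material proxy effect therefore needs imbalance between the 475 depressed participants and the other 425.

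**5. The severity target.** The AUC figures describe the classifier. For severity, the share of variance that a null IGF-1 picks up is (r × correlation of severity with the covariate)². The second correlation is not in the documents either, so no number is given.

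**6. Whether the gain is estimable.** Assume a base R² of 0.10 and a one-degree-of-freedom F test with N = 870. For an added R² of 1%, f² = 0.01/(0.90 − 0.01) = 0.0112, non-centrality 870 × 0.0112 = 9.8, and power is 0.88. For 0.5% and 2% it is 0.60 and 0.99. This is an ordinary regression test, not the cross-validated gain, and serves only as a guide.

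**The case against.** **This is a condensed article.** Benchmark models are often left to the full protocol or the SAP, neither of which is shown, and a base model may be specified there. Age and gender are already named as confounders. That limits the point but does not remove it. The article itself fixes the predictors, the attribution hypothesis and the way it is judged, and that combination cannot separate IGF-1 from what it tracks. BMI is missing from the confounder list.

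**Planned data analyses comes close to a remedy.** The sequential model judges whether further data are worth collecting, so it would be wrong to say that the plan has no comparison at all. But no first step of age, sex and BMI is named. Assessing modalities separately shows how each does alone, not what the biomarkers add. The expert rating serves the one-year algorithm.

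**Stronger readings are tempting but unsupported.**

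- A reader might infer that the cohorts are known to be unbalanced. The article only describes no matching and different selection. Most participants, depressed or not, are to come from GP offices.
- A reader might infer that younger, leaner healthy controls create a large age gap. Step 4 shows that 50 people cannot.
- A reader might extend the proxy argument to the whole panel. The article's statement concerns IGF-1; nothing comparable is cited here for AAT-1 or HRV.
- A reader might want the incremental gain to replace the primary outcome. That is a debatable trade-off, since the stated aim is to develop an algorithm, and waist and smoking may lie on the pathway under study.

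**Conclusion.** The point holds in a limited form. As written, the plan can credit IGF-1 with information a GP already has, and no analysis named in the article would reveal it. The mechanism follows from the article's own account of IGF-1. Its size in this study cannot be derived: it is zero without imbalance, negligible if only the healthy controls differ, and AUC 0.51 to 0.64 for a null IGF-1 over the assumed range of r (0.2 to 0.63) and d (0.25 to 0.8). The documents do not show that the result will be biased, and they do not show that the panel lacks value. What is missing is the comparison that would settle how much the markers add. This should be changed before analysis; recruitment is expected to run until October 2027, so there is time to prespecify it.

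**What to change.** In Primary outcome and Planned data analyses, keep the primary algorithm and add a prespecified base model of age, sex and BMI, fitted in the same leave-site-out nested cross-validation. Add waist and smoking only in a sensitivity version, because the protocol treats lifestyle as mediating. Fit the base model with and without IGF-1, AAT-1 and HRV, and report the out-of-fold gain with an interval: as R² or prediction error for severity, and as AUC for the classifier. Base any statement that the markers facilitate diagnosis on that gain. Say also how the named confounders enter the algorithms.

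The cost is one extra model. BMI, waist and smoking are already collected (Medical examinations), as are socio-demographic data (Table 2), so no new patients or measurements are needed. The downside is a less favourable headline, since an increment will usually be smaller than total accuracy.

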#### Secondary outcomes

Furthermore, we will implement a prospective algorithm predicting the severity of the participants' depressive symptomatology after one year. The results will be compared with the expertrating conducted at baseline. To ensure generalizability we will test the cross-sectional algorithm on the follow-up data. Further we will conduct a structural equation model (SEM) analysis at inclusion to better understand the underlying mechanisms that drive unipolar depression. Unsupervised cluster algorithms will be used to detect biomarker driven subtypes.

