### Study timeline

We will perform a follow-up assessment 4 weeks after the participants’ inclusion into the study, and then annually for a total of 5 years, as indicated in Table 2.

**Table 2 Tab2:** Study assessment overview

	Study inclusion	After 4 weeks	Yearly follow up until 5 years
Observer rating	MADRS, GAF SIMPAQ, expert rating, SCID-CV	MADRS, GAF SIMPAQ	MADRS, GAF SIMPAQ, expert rating,
Self-rating questionnaires	Large questionnaire profile^1^	Small questionnaire profile^2^	Large questionnaire profile^1^
HRV measurements	At least 10 min (5 min supine/sitting each)	At least 10 min (5 min supine/sitting each)	At least 10 min (5 min supine/sitting each)
Bioimpedance scale	Tanita scale	Tanita scale	Tanita Scale
Laboratory assessments	Multiplex analysis, blood collection^3^	Multiplex analysis, blood collection^3^	Blood collection^3^
Vital parameters	Blood pressure, temperature, pulse	Blood pressure, temperature, pulse	Blood pressure, temperature, pulse

Large questionnaire profile^1^: socio-demographic data, family history, medical history, PHQ-9, PHQ-15, MCTQ, GAD-7, postal code, PID5BF + M, WHO-DAS, FEV, CTS, CTQ, PC-PTSD, PACIC, FEV, WHO-5, LSNS 6, BRS, UCLA LS 3, SSD-12, IDS-SR small questionnaire profile^2^: HTQ, PHQ-9, PHQ-15, MCTQ, GAD-7, WHO-DAS, FEV, SSD-12, IDS-SR Blood Collection^*3*^: fasting glucose, triglycerides, morning cortisol, CRP, AAT-1, IGF-1, cortisol, TSH, complete blood count, HbA1c, liver values

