### Medical examinations

#### Clinical assessments

Depressive symptomatology is assessed using self-rated instruments (PHQ-9), the Inventory of Depressive Symptomatology (IDS-SR) [73] and observer ratings (MADRS) at inclusion and each follow-up [74]. At inclusion functionality will be rated using the General Assessment of Functioning (GAF) [75, 76]. To precisely detect possible exclusion criteria a SCID-5-CV rating is performed at study inclusion. All assessments are done by experienced and trained raters [77]. Furthermore, a rating is conducted where the raters need to describe their own impression concerning prognosis and give an estimate concerning the disease trajectory.

The abdominal circumference, as well as the hip circumference are measured standing with the upper body free with a measuring tape according to the guidelines of the WHO [78]. Blood pressure measurement (systolic, diastolic) and pulse is performed after 3–5 min of rest while sitting [79]. In addition, body temperature is determined with a tympanic thermometer in the morning [80].

Heart rate and HRV are measured using special chest straps (EcgMove4) from Movisens (Movisens GmbH), which determines body position. A HRV measurement is performed at each follow-up. The participants are kindly asked to be in an upright position for 5 min and lie for 5 min while breathing at a normal pace to achieve a resting state measurement [81]. If needed, participants can take breaks. Each participant should wear the belt at least for 10 min. Healthy controls will wear the belt for 24 h5 if possible. Blood is drawn between 8:00–10:00 in the mornings and analyzed at the Institute of Laboratory Medicine (LMU Hospital). Specifically, glucose, liver values, cholesterol (HDL and LDL), triglycerides, cortisol, TSH, AAT-1, IGF-1, CRP, and complete blood count are measured. The participants are asked not to smoke and to conduct an overnight fast before the examination. If participants are additionally willing to take part in the Munich Mental Health Biobank Project (MMBH), [82] further blood is drawn (9 ml Serum, 9 ml Li-Heparin, 7.5 ml EDTA, 2.4 ml RNA Extract) and stored at – 80 °C. Further analysis of MMHB blood samples is possible in following projects.

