### Power calculation

An a priori power analysis was performed to calculate the minimum of needed study participants to conduct a SEM analysis. We assumed a power (1-β) of 0.90 with an effect size of 0.15 and an alpha of 0.05. With these settings a sample size of at least 870 was required to achieve a robust model with 5 latent variables. With estimated screening failures of slightly less than 10% (e.g. development of bipolar disorder in the further course, or with inclusion concealment of a dependence illness) we aim to recruit 950 participants at inclusion. We aim to recruit a sample size of 475 patients with depression and 475 participants without depression. Recruitment in the project presented here will end when the sample size of 950 subjects is reached. Also, this is a sufficient number of participants for machine learning algorithms [106].

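### Testing the inclusion-trained algorithm on later visits of the same participants shows temporal stability, not generalizability, unless held-out folds are kept

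*Protocol article*

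**What the plan says.** The Primary outcome section describes an algorithm learned on the inclusion data: "Supervised algorithms like decision trees and support vector machines will be used to determine which factors drive the severity of depression at inclusion". Its inputs are the routine blood markers and HRV, with single questionnaire items only if needed.

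Secondary outcomes then names a test of that algorithm and its purpose: "To ensure generalizability we will test the cross-sectional algorithm on the follow-up data". The section Study timeline defines where the follow-up data come from: "We will perform a follow-up assessment 4 weeks after the participants’ inclusion into the study, and then annually for a total of 5 years". They are repeat visits of the enrolled participants, and no separate cohort is named for this test. Both predictors and outcome are measured again. On HRV, Clinical assessments says "A HRV measurement is performed at each follow-up", and Table 2 repeats the blood collection at every visit. On outcome, the article says "We will use the PHQ-9 and the MADRS at baseline and follow-up to measure changes in depressive symptomatology".

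Planned data analyses separately specifies leave-site-out nested cross-validation in each model, for algorithm selection and for performance assessment, and says of it: "This mitigates the risk of overfitting and ensures generalizability". The Discussion, in the part on developing the algorithm, adds that a further study would be needed to validate the model.

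**The concern.** Generalizability here has to mean performance in patients the model has not seen, because the stated goal is a tool for general practitioners. A later visit of a training participant is not a new patient. Blood values and HRV may resemble the same person's earlier values, and depression often persists. A model that has partly memorised individuals at inclusion can then recognise them at follow-up and be right for that reason alone.

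The article does not say which fitted model is applied to the follow-up records. If it is one final model fitted to all participants, an overfitted algorithm can pass this test, and a result labelled as generalizability would be reported for the primary-outcome algorithm without supporting that label.

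**Working it through.** The sentence at issue carries no figure, so there is nothing of the plan's to reproduce. The power calculation concerns the structural equation model and does not enter here. The check asks what the test would show if the markers carried no information at all.

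**Inputs from the article.** N = 950, split evenly ("We aim to recruit a sample size of 475 patients with depression and 475 participants without depression"); 6 sites, the upper end of the stated goal of 5 to 6; support vector machines and decision trees as named learners.

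**Assumptions (the article gives no values).** 20 markers; correlation rx between a person's marker values at two visits; correlation ry between a person's severity at two visits.

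**Model.** Each e is independent noise, and markers are independent of severity at every visit.

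- Markers: X1 = rx·X0 + √(1 − rx²)·e
- Severity: S1 = ry·S0 + √(1 − ry²)·e
- Depressed or not: S split at its median

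Each learner is trained on (X0, outcome at inclusion) and scored on (X1, outcome at follow-up). The true AUC is 0.50 and the true correlation is 0.

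**Same participants at follow-up, depressed or not (mean AUC over 15 to 20 replicates):**

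| rx | ry | Logistic | Depth-5 tree | RBF-SVM |
|---|---|---|---|---|
| 0.6 | 0.6 | 0.522 | 0.507 | 0.555 |
| 0.8 | 0.4 | 0.518 | 0.510 | 0.567 |
| 0.8 | 0.6 | 0.526 | 0.515 | 0.601 |
| 0.8 | 0.8 | 0.536 | 0.525 | 0.649 |
| 0.9 | 0.7 | 0.530 | 0.539 | 0.663 |
| 0 | 0.6 | 0.499 | 0.498 | 0.501 |
| 0.8 | 0 | 0.501 | 0.497 | 0.504 |

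At rx = 0.8 and ry = 0.6 a random forest gives 0.599, a tuned SVM 0.605 and a tuned single tree 0.522. The last two rows show that both kinds of stability are needed.

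**Same setting (0.8, 0.6), participant's site left out of training, scored on follow-up:** logistic 0.502, depth-5 tree 0.505, RBF-SVM 0.494, random forest 0.493. The spurious accuracy is gone.

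**Continuous severity, same participants (correlation of predicted with observed):**

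| rx | ry | Ridge | Depth-5 tree | RBF-SVR | Random forest |
|---|---|---|---|---|---|
| 0.6 | 0.4 | 0.03 | 0.01 | 0.09 | 0.07 |
| 0.8 | 0.6 | 0.06 | 0.05 | 0.28 | 0.20 |
| 0.9 | 0.8 | 0.10 | 0.10 | 0.49 | 0.44 |

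With the site held out, every correlation lies between −0.04 and 0.03.

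**Sensitivity to the number of markers (ridge classifier, n = 870).** Here a share of labels persists and the rest are redrawn.

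- Share 0.8 (label agreement 0.8 + 0.2 × 0.5 = 0.90 with an even redraw) and within-person marker correlation 0.7 to 0.9: AUC 0.55 to 0.56 with 20 markers, 0.58 to 0.60 with 60 and 0.60 to 0.64 with 100.
- Share 0.6 (agreement 0.6 + 0.4 × 0.5 = 0.80) and marker correlation 0.5: 0.52, 0.54 and 0.56.
- Each person scored by a model that never saw that person (checked for the first of these settings): 0.49 to 0.50.

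The larger marker sets are relevant only if the tested algorithm is the classifier that uses all relevant data. The severity algorithm has a narrower input list.

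**The case against.** The strongest reply is that the plan already tests new people. Leave-site-out nested cross-validation is specified for performance assessment as well as model selection, and in each model. A reader might infer from the follow-up sentence that the plan has no valid test of generalizability, or that this test is its only proof. The documents do not support that: the held-out-site result stands, and the Discussion concedes that a further validation study is necessary. Nor does the article call the follow-up result a replication.

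It can also be said that applying cross-validation in each model leaves room for the held-out folds to carry over to follow-up, and that such detail belongs in a fuller document. This is fair as far as it goes. The article does not say that a model refitted to everyone will be used, and with the folds kept the artefact disappears. But the stated purpose is still wrong for the stated data. Even with folds kept, what the follow-up visits add beyond the held-out-site result is evidence on stability over time.

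A reader might further infer that spurious accuracy is certain. It is not. It needs stable markers and stable severity over intervals of 4 weeks to 5 years, for which the article gives no figures. It also depends on the learner: with 20 markers it is small for linear models and single trees, and clear for an RBF-SVM or a random forest. SVMs are among the named candidates, so the clear case is within the plan's scope.

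**Conclusion.** The point holds in a limited form. The follow-up test is wrongly labelled: it uses later visits of training participants and cannot by itself show performance in new people. That conclusion rests on the article's own description and on no simulation.

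The size of possible false credit does rest on assumptions. With useless markers, a model fitted to everyone, marker stability of about 0.5 to 0.9 and persisting depression status, the AUC is about 0.52 to 0.56 for linear models with 20 markers. For an RBF-SVM it is about 0.56 to 0.66, and it could be higher under stronger stability. It is at chance if either kind of stability is absent or the participant's site was held out.

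Severity is moderate: one secondary test of the primary algorithm is affected, and the leave-site-out assessment at inclusion is untouched.

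**What to change.** In Secondary outcomes, state that each participant's follow-up record is scored only by the outer-fold model from which that participant's site was held out, and call the result temporal stability. Base any claim of generalizability on the leave-site-out result at inclusion or on participants not used in training.

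This takes a sentence or two and needs no new visits or data, because the leave-site-out scheme already produces the fold models. The cost is that the reported follow-up figure may be less favourable.
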